## Abstract

**Background:**

Children of substance-involved mothers are at especially high risk for exposure to adverse childhood experiences (ACEs) and poor mental health and development. Early interventions that support mothers, children, and the mother-child relationship have the greatest potential to reduce exposure to early adversity and the mental health problems associated with these exposures. Currently, there is a lack of evidence from the real-world setting demonstrating effectiveness and return on investment for intervention programs that focus on the mother-child relationship in children of substance-involved mothers.

**Methods:**

One hundred substance-involved pregnant and/or parenting women with children between the ages of 0–6 years old will be recruited through the Breaking the Cycle and Maxxine Wright intervention programs, in Toronto, Ontario, Canada and Surrey, British Columbia, Canada, respectively. Children’s socioemotional development and exposure to risk and protective factors, mothers’ mental health and history of ACEs, and mother-child relationship quality will be assessed in both intervention programs. Assessments will occur at three time points: pre-intervention, 12-, and 24-months after engagement in the intervention program.

**Discussion:**

There is a pressing need to identify interventions that promote the mental health of infants and young children exposed to early adversity. Bringing together an inter-disciplinary research team and community partners, this study aligns with national strategies to establish strong evidence for infant mental health interventions that reduce child exposure to ACEs and support the mother-child relationship. This study was registered with clinicaltrials.gov (NCT05768815) on March 14, 2023.

**Supplementary Information:**

The online version contains supplementary material available at 10.1186/s40359-023-01484-w.

## Background

 Exposure to Adverse Childhood Experiences (ACEs), including abuse, neglect, and family dysfunction, is one of the top threats to children’s mental health and development [1, 2]. Children exposed to ACEs are far more likely than children not exposed to experience socioemotional difficulties and post-traumatic stress [3], both of which are precursors to mental illness in adulthood [1, 4–7]. Most children (57.8%) experience at least one ACE in their childhood [8]; however, children exposed to cumulative adversity are at highest risk of poor long-term health and mental health outcomes [1]. Children of substance-involved mothers are at especially high risk for exposure to cumulative ACEs [9] and their developmental consequences, given that maternal substance use often co-occurs with other risk factors, including household violence, intergenerational trauma, poverty, lack of social support, and poor maternal mental health [10]. Exposure to ACEs can thus be intergenerational in nature, whereby mothers who experienced a lack of safety and support in their own childhood struggle to provide nurturance to their children [11–13]. As such, early intervention programs are needed to mitigate poor outcomes for young children of substance-involved mothers.

The first five years of a child’s life establish the building blocks for physical and mental health across the lifespan, with the steepest changes in brain development occurring during this critical period. Exposure to ACEs, particularly in the first five years of life, has a cascading negative impact on brain development [14], increasing the risk for mental health challenges across the lifespan. Thus, intervening to disrupt the negative cascade associated with exposure to ACEs in young children is critical for mitigating poor outcomes and fostering optimal development [15, 16]. It can also attenuate the lag in child development typically observed in children of substance-involved mothers [16]. Additionally, there is growing evidence that interventions during the early years not only benefit families, but also yield long-term economic returns for society [15, 17]. At the population level, it is estimated that a 10% reduction in ACE prevalence could lead to an annual cost savings of up to $105 billion USD and an annual reduction of up to 3 million ACE-attributable disability-adjusted life years [18]. Despite the broad impact of these findings, the mental health of infants, young children, and their families living in contexts of high psychosocial risk has been historically underprioritized [19] suggesting the need for prevention and intervention approaches.

Interventions that simultaneously support mothers, children, and the mother-child relationship have the greatest potential to reduce mental health problems associated with exposure to early adversity [18, 19]. Specifically, interventions that support mothers’ stability by addressing trauma and substance use problems and provide programming related to parenting, healthy relationships, and family violence are the most promising for reducing childhood adversity and promoting optimal child development [20–22]. Currently, there is a lack of knowledge and evidence from real-world settings demonstrating effectiveness and return on investment for intervention programs that focus on the mother-child relationship in children of substance-involved mothers to reduce adversity and improve infant mental health outcomes. The current study aims to address this knowledge gap by comparing the effectiveness of two intervention programs for substance-involved mothers and their young children being delivered in Canada.

### Objective

This paper describes the protocol for a comparative effectiveness study of the Breaking the Cycle (BTC) and Maxxine Wright Community Health Centre (MWCHC) intervention programs offered to substance-involved mothers and their young children (0–6 years). This study will explore the effectiveness of the mother-child focused BTC intervention as compared to the mother-focused program of the MWCHC program. More specifically, the study aims to establish the comparative effectiveness and mechanisms of change of the infant mental health components at BTC, as well as estimate the long-term social return on investment (SROI) of BTC. The key research questions it aims to answer are:1a: Do children at BTC demonstrate enhanced infant mental health compared to children at MWCHC up to 2 years post-intervention?1b: Are decreases in exposure to child ACEs, maternal stress, and mental health symptoms and increases in environment scores, parenting attitudes, and mother-child relationship scores greater among mothers at BTC than at MWCHC between pre-treatment and 24-months after engagement?1c: Are lower exposure to psychosocial risk, lower maternal mental health difficulties, and lower maternal stress at baseline associated with enhanced infant mental health scores over time?2a: Are the associations between treatment dose and infant mental health scores mediated by parenting attitudes and the quality of the mother-child relationship?2b: Does child exposure to psychosocial risk moderate the association between treatment dose and child outcomes?3: What is the estimated long-term SROI of the combined mother-child focus and infant mental health components of the BTC program?

## Methods

### Design

This intervention study is designed as a non-randomized, non-equivalent, comparison study with two equally allocated parallel groups: the BTC intervention group and the MWCHC intervention group. Given that the two intervention programs serve a similar demographic of women, researchers will compare the BTC and MWCHC groups to establish the comparative effectiveness and mechanisms of change of the additional infant mental health component of BTC. The study has been approved by the University of Ottawa Research Ethics Board (REB # H-02-23-8940) and is registered with ClinicalTrials.gov (NCT05768815). All research is performed in accordance with relevant guidelines and regulations. This protocol paper adheres to the SPIRIT guidelines (see Additional file 1).

### Participants

Participants will comprise substance-involved pregnant and/or parenting women with children between the ages of 0–6 years old. We aim to recruit a total of 100 participants: 50 through the BTC intervention and 50 through the MWCHC intervention. To be eligible for the study, participants must: be receiving services at either BTC or MWCHC; have a child under the age of 6 years; and be able to complete the study questionnaires in English. There are no exclusion criteria for participation in this study.

### Recruitment

Mothers will be invited to participate in the study by BTC and MWCHC clinicians providing services at the community-based intervention programs. The clinicians will introduce the research to potential participants within six weeks following their first intake meeting and before receiving any services (e.g., counselling, group participation). Women will be assured that whether they participate or not in the study will not affect the clinical services they receive at either program. This lag time is essential to build trust and rapport with the mothers [23]. Mothers who are interested in participating in the research will be contacted by a community-based researcher (CBR), embedded within each of the intervention programs, who will further explain the research and ask for consent to participate, to be contacted for follow-ups, and to access their clinical file to obtain demographic and other information about psychosocial risk exposure through a retrospective file review. This is a trauma-informed approach to obtaining information whereby participants are not obligated to report information that they have already shared clinically [23].

### Interventions

#### Breaking the Cycle

BTC is a prevention and early intervention program in Toronto, Canada, serving substance-involved pregnant and/or parenting women with children under six years of age. Established by the Canadian Mothercraft Society in 1995, BTC is funded by the Community Action Program for Children and the Canadian Prenatal Nutrition Program through the Public Health Agency of Canada. BTC uses several theoretical frameworks, including developmental theory (i.e., consideration of the combined contributions of both the prenatal and postnatal environments), attachment theory (i.e., child’s cognitive and emotional sense of self and others is developed within the emotional relationship between infants and their primary caregivers), trauma theory (i.e., people who experience trauma are profoundly impacted by those experiences), relational theory (i.e., people grow through relationships with others), and harm reduction (i.e., reducing negative social and/or physical consequences associated with substance use) [24]. BTC provides three components that act synergistically: (a) individualized services for mothers, (b) individualized services for children, and (c) relational interventions that enhance the mother-child relationship and promote infant mental health. Primary services offered include mental health counselling, addictions services, health and medical services, basic needs support, probation and parole services, parenting services, pregnancy outreach program, childcare, and a developmental clinic [24, 25]. In 2004, BTC was recognized by the United Nations as an exemplary program serving pregnant and parenting women who are substance-involved, and their young children [26]. BTC has documented its knowledge creation through evaluation reports [25, 27], scholarly publications [28–30], and a national implementation of its interpersonal violence intervention [31–35].

#### Maxxine Wright

Founded in 2005 and located in Surrey, British Columbia, the MWCHC supports substance-involved women who are pregnant and/or have young children. Women do not need to have children in their care to receive services. MWCHC is a partnership between the Fraser Health Authority, Atira Women’s Resource Society, and the BC Ministry for Children and Family Development. MWCHC addresses maternal substance use and exposure to violence through a multidisciplinary approach. This includes the following philosophical/theoretical approaches: supportive and woman-centered (i.e., creating a safe and supportive environment for women), harm reduction (i.e., recognizing recovery as a long process and a stepping stone toward wellness), trauma-informed (i.e., recognizing that many women have experienced serious trauma), multidisciplinary and wraparound (i.e., providing wraparound health care and social support services to address women’s and children’s needs), health-centered (i.e., providing health care expertise and positive experiences for women and their infants/children), and relational (i.e., focusing on respectful, non-judgmental relationships and compassion) [36]. Primary services offered include addiction counselling, primary health care, and opiod agonist therapy. Within MWCHC, child-focused services are limited to primary health care (e.g., well baby checks, immunizations, referrals for developmental services, growth tracking, and childcare) and do not address the mother-child relationship.

Both the BTC and MWCHC intervention programs are considered integrated maternal substance-use programs in that they offer supports in additional to maternal substance use treatment [36]. Both programs provide services to mothers and their children. For example, both intervention programs have access to childcare, instrumental parenting support, and developmental education. The main difference between the two intervention programs is that BTC uses an infant mental health framework and provides therapeutic supports (e.g., home visitations) to support child development and the parent-child relationship. Given that MWCHC serves a similar demographic of women as BTC but does not focus on infant mental health, they will serve as a comparison site. Table 1 below presents an overview of the services offered by BTC and MWCHC.

**Table 1 Tab1:** Comparison of services between Breaking the Cycle (BTC) and Maxxine Wright Community Health Centre (MWCHC)

Service feature		Service approach	BTC	MWCHC
Target population	Pregnant or parenting women with substance use difficulties	Mother-focused	Yes (0-6 years)	Yes (0-6 years)
Structure	Ongoing relationship with the child	Mother-focused	Yes	Yes
	Plan to parent	Infant Mental Health	Yes	No
	Comprehensive, wrap-around approach	Mother-focused	Yes	Yes
	Women-centered, trauma-informed	Mother-focused	Yes	Yes
	Infant Mental Health Frameworks	Infant Mental Health	Yes	No
Basic needs support	Food, clothing, transportation	Mother-focused	Yes	Yes
	Childcare	Mother-focused	Yes	Yes
Broader Services	Individual Family Advocacy	Mother-focused	Yes	Yes
	Case Management/Service Coordination	Mother-focused	Yes	Yes
	Primary Health Care Services (mother/child)	Mother-focused	Yes	Yes
Addiction Services	Individual Addictions Services	Mother-focused	Yes	Yes
	Relapse Prevention Group	Mother-focused	Yes	Yes
	Recovery Support Group	Mother-focused	Yes	Yes
	Trauma and Interpersonal Violence Group	Mother-focused	Yes	Yes
Mental Health	Individual Mental Health Counselling	Mother-focused	Yes	Yes
	Individual Trauma Counselling	Mother-focused	Yes	Yes
	Life Skills/Emotion Coping Group	Mother-focused	Yes	Yes
Prenatal Services	Pregnancy Outreach Program	Mother-focused	Yes	Yes
	Prenatal care Services	Mother-focused	Yes	Yes
Instrumental Parenting Support	Basic Parenting support, child management, developmental education	Mother-focused	Yes	Yes
Child Development Supports	Annual Developmental Assessments	Infant Mental Health	Yes	No
	Developmental Screening (annual)	Infant Mental Health	Yes	Yes
	Individualized Developmental Therapy Plan	Infant Mental Health	Yes	No
	Home-visitation focused on child development	Infant Mental Health	Yes	No
	Therapeutic childcare	Infant Mental Health	Yes	No
Mother-child Relationship Support	Individual parenting support/Interaction Guidance	Infant Mental Health	Yes	No
	New Mom’s Support Group (Infant 0-6 months)	Infant Mental Health	Yes	No
	Parent-Child Mother Goose Program	Infant Mental Health	Yes	No
	Learning through Play Group (infant: 6+months)	Infant Mental Health	Yes	No
	Cooking Healthy Together Group	Infant Mental Health	Yes	No
	Parenting Group Support	Infant Mental Health	Yes	Yes

### Primary outcome measures

Informed by the gold standard for assessing and classifying mental health difficulties in the early years (DC: 0–5 [37]), we will use two domains to assess infant/early childhood mental health: (1) socio-emotional functioning and (2) developmental functioning. Measures that provide a diagnosis of mental and physical health problems are not used in the current study due to the infrequency and reliability of these data.

#### Child’s socio-emotional functioning

Mothers will complete the Ages & Stages Questionnaire: Social-Emotional, Second Edition (ASQ-SE-2) [38] version for children. The ASQ-SE-2 measures a child’s self-regulation, compliance, social-communication, adaptive functioning, independence, and relationships. The version used for the present study consists of a total of 23 items using a three-point scale that includes the option for mothers to indicate whether they feel the behavior is of concern. The ASQ-SE-2 shows good psychometric properties and is widely used in early intervention and mental health programs [39].

#### Child’s developmental functioning

Mothers will complete the Ages & Stages Questionnaire, Third Edition (ASQ-3) version [40]. The ASQ-3 assesses a child’s development across five domains: communication, gross motor, fine motor, problem solving, and personal-social skills. The version used for the present study consists of a total of 36 items requiring parents to indicate whether their baby exhibits the behaviour regularly, sometimes, or not yet. The ASQ-3 has strong psychometrics properties and is an internationally used developmental screening measure [41].

### Secondary outcome measures

#### Child’s exposure to risk and protective factors

To assess children’s exposure to risk (e.g., ACEs, poverty, maternal mental illness) and protective factors (e.g., family social support, childcare, community supports), a cumulative measure designed by Bondi et al. (2020) will be used [42]. These measures identify risk and protective factors, including ACEs, for children of substance-involved mothers specifically and were established using data from previous clients at BTC. The measures can be used with children exposed to varying levels of risk and allitems are coded dichotomously (yes or no).

#### Maternal behaviour

To assess the sensitivity of maternal behaviour from a 10-minute in vivo mother-child interaction, the CBRs at each site will use the Maternal Behavior Q-Set (MBQS), Brief Version [43]. The 25 items are centered on parents’ responses to their child’s behaviors and signals. The brief version of the MBQS has been validated with mother-child dyads and has indicated appropriate psychometric characteristics [43, 44].

#### Maternal stress

To assess maternal stress, mothers will complete the Parenting Stress Index (PSI) Short Form [45]. This scale comprises 36 items that are rated on a 5-point Likert scale of agreement. The items are grouped into three domains: parental distress, parent-child dysfunctional interaction, and difficult child, creating a total stress scale when combined. The empirical validity of the PSI Short Form has been well established.

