### Statistical analysis

All data analyses will be conducted in SAS and Mplus. For research question 1a, linear mixed models will be used to model the change in each of the primary outcomes from baseline to 24-months post-engagement for the BTC and MWCHC groups, controlling for demographic variables that potentially differ at baseline (e.g., maternal age, socioeconomic status, maternal ACEs). Slopes of the two groups will be compared using an interaction term. Linear mixed models can accommodate participants with missing observations [20]. For research question 1b, we will analyze secondary outcomes with a similar approach. For research question 1c, we will conduct regression analyses to predict which risk and protective factors identified at baseline predict change in the primary outcome for the BTC group.

For research question 2, we will conduct a series of mediation (indirect effects) and moderator analyses (interaction effects) for the BTC group, with time in treatment as the independent variable and infant mental health outcomes at 24 months as the dependent variable. Mediator (i.e., maternal behaviour, parenting attitudes, and maternal stress) and moderator (i.e., psychosocial risk) variables at 12 months will be used in all analyses.

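### If maternal stress enters the question 2 mediation as the PSI total, two of its three domains are the mother's ratings of the child or dyad and overlap with the mother-rated ASQ-SE-2 outcome; the mediator lists also disagree

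*Protocol article*

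**What the plan says.** All references are to the protocol article.

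- **Instrument.** The Maternal stress section names one measure: "To assess maternal stress, mothers will complete the Parenting Stress Index (PSI) Short Form". It then says: "The items are grouped into three domains: parental distress, parent-child dysfunctional interaction, and difficult child, creating a total stress scale when combined". No other combined stress score is described, and no sentence states which PSI score enters which model.
- **Child outcome.** The same mother completes the ASQ-SE-2, one of the two primary outcome measures. It covers "self-regulation, compliance, social-communication, adaptive functioning, independence, and relationships". She also completes the ASQ-3, which covers communication, motor, problem-solving and personal-social skills.
- **Question 1c.** The Objective asks whether, among other factors, "lower maternal stress at baseline associated with enhanced infant mental health scores over time". The Statistical analysis section answers this with regressions to "predict which risk and protective factors identified at baseline predict change in the primary outcome for the BTC group".
- **Question 2, as asked.** Question 2a in the Objective asks whether the link between treatment dose and infant mental health is "mediated by parenting attitudes and the quality of the mother-child relationship".
- **Question 2, as analysed.** The Statistical analysis section runs the mediation in the BTC group "with time in treatment as the independent variable and infant mental health outcomes at 24 months as the dependent variable". The mediators are taken at 12 months and listed as: "Mediator (i.e., maternal behaviour, parenting attitudes, and maternal stress". No earlier child score is named as a covariate.

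**The concern.** A mediator should be a different thing from the outcome it is meant to explain. Here the 12-month mediator, read as the PSI total, contains the mother's rating of how difficult her child is and of how badly the two interact. The 24-month outcome includes the same mother's rating of the child's self-regulation, compliance and relationships. A child whose behaviour is stable, rated twice by one informant, will link the two even if the mother's own distress has no role.

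The interaction domain also overlaps with mother-child relationship quality, which question 2a names as a mediator in its own right and which the community-based researchers observe with the MBQS.

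The result has a further use. The plan for question 3 builds its theory of change partly on the mechanisms found in question 2, so a spurious stress pathway could be carried into the economic model.

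**Working it through.** **1. The plan's own figure.** The document gives no figure on this point. Its only statistical result is the power for question 1a. With 34 per group, d = 0.70 and two-sided alpha 0.05, the noncentrality is 0.70 × √(34/2) = 2.89 on 66 degrees of freedom. Power is 81.2% (stated 81.1%), and 34/0.70 rounds up to 49 per group. It reproduces, and nothing below changes it.

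**2. The two mediator lists.**

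| Objective, question 2a | Statistical analysis, question 2 |
|---|---|
| Parenting attitudes | Parenting attitudes |
| Mother-child relationship quality | Maternal behaviour (plausibly the same construct, via the MBQS) |
| (none) | Maternal stress |

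Stress is analysed as a mediator without a research question that asks for it.

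**3. Size in question 2 (illustration; every correlation is an assumption).** All variables are standardised. Dose X acts on 12-month child state C12 with coefficient 0.4. C12 carries to 24 months, C24, with coefficient 0.6, and there is no other path. The total effect is 0.4 × 0.6 = 0.24. Parental distress is pure noise. The difficult-child and interaction domains each load λ on C12. The PSI total T is the unweighted sum of the three domains.

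- Path from X to T: 2λ × 0.4 = 0.8λ.
- Covariance of T and C24 given X: 2λ × 0.6 × (1 − 0.16) = 1.008λ.
- Variance of T given X: 3 + 2λ² − (0.8λ)² = 3 + 1.36λ².
- False indirect effect: 0.8λ × 1.008λ / (3 + 1.36λ²).

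| λ | False indirect effect | Share of 0.24 |
|---|---|---|
| 0.3 | 0.0726 / 3.1224 = 0.023 | 10% |
| 0.5 | 0.2016 / 3.3400 = 0.060 | 25% |
| 0.7 | 0.3951 / 3.6664 = 0.108 | 45% |

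A simulation with 400,000 records per setting agrees (9.7%, 25.4%, 44.6%). With parental distress alone as the mediator, the share is 0%. With the total as mediator and C12 adjusted for without measurement error, the false indirect effect is also 0. These are large-sample biases, not false-positive rates.

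**4. Question 1c.** The outcome here is change. Let a child or dyad domain correlate r₀ with the baseline child score and r₂₄ with the 24-month score, with equal variances and stability s. Its correlation with change is (r₂₄ − r₀) / √(2(1 − s)).

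- If r₂₄ = r₀, this is 0.
- If r₀ = 0.5, s = 0.6 and r₂₄ = 0.5 × 0.6 = 0.3, it is −0.2/√0.8 = −0.22. With scores coded so that higher is worse, families with higher baseline stress scores would appear to improve more, the opposite of what question 1c expects.

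So the overlap works through the baseline child score, and its direction is not fixed.

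**The case against.** **The document does not say that the total is used.** That is true. The Maternal stress section describes an instrument, and an analysis plan that is not shown could specify the Parental Distress domain or adjust for earlier child scores. The point is therefore conditional on the natural reading. The mismatch between the two mediator lists is not conditional: both are in the published text, and a separate plan cannot make them agree.

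**The overlap is mainly with one outcome.** This also stands. The study is powered on ASQ-3, whose content is largely developmental skills. There the problem is mainly the shared rater.

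**A reader might infer that false findings are likely in both 1c and 2.** Assume parental distress has zero correlation with later ASQ-SE-2, the other two domains correlate r = 0.3 to 0.5 with it, and the domains intercorrelate 0.5. The total then correlates 2r/√6 = 0.24 to 0.41 with the outcome. By Fisher's z this is significant in about 40% to 84% of studies with n = 50, or 29% to 69% with n = 35. The arithmetic is right, but it does not support that inference for three reasons:

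- It models correlation with a later level, while question 1c models change.
- It tests one mediator-outcome correlation. An indirect effect also needs a path from dose to the mediator, and conditioning on dose.
- It makes parental distress a suppressor, not an inert variable: given the other two domains its standardised coefficient is −r, that is −0.3 to −0.5.

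**Parental Distress is still rated by the same mother.** Correct. Changing the domain removes the overlap in content but not the shared rater.

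**Conclusion.** The point holds for research question 2 with ASQ-SE-2, on condition that the PSI total is the stress score used. It should be settled before the mediation is run. For ASQ-3 the concern is mainly shared rater. For question 1c it is a matter of consistency, because the direction of any bias is uncertain.

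The false mediated share of 10% to 45% shows that the mechanism can matter. It rests on assumed loadings of 0.3 to 0.7, a dose effect of 0.4 and stability of 0.6, none of which comes from the documents, so it is not an estimate for this study. The effect on the question 3 benefit-cost ratio cannot be sized. Question 1a and the sample size are untouched.

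Separately, and without any assumption, the Objective and the Statistical analysis section name different mediators.

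**What to change.** 1. State which PSI score is used. In question 2, and for consistency in 1c, take the Parental Distress domain as the maternal stress variable and report the PSI total as a sensitivity analysis.
2. Adjust the 24-month models in question 2 for the baseline child score. This handles differences between children that existed before treatment. It does not handle child change produced by treatment in the first 12 months, which is the route in the illustration; the choice of domain deals with that. The 12-month child score lies downstream of treatment, so adjustment for it belongs at most in a sensitivity analysis.
3. Make the mediator lists agree: either drop maternal stress from the Statistical analysis section, or add it to question 2a as Parental Distress.

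**Cost.** Wording only for items 1 and 3, since the domain score comes from the 36 items already collected. The scale is shorter and slightly less reliable, and shared-rater bias is reduced but not removed. Item 2 uses one more degree of freedom in a group of about 35 completers (50 × 0.70) and needs a baseline child score, which would be missing for any child not yet born at enrolment.
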